### Sample size

The sample size for this study was based on the study by King [20] cited earlier, reporting a 20% difference in adherence to physical activity between a group and home based intervention at 12 months. Assuming a standard deviation of 35% based on this study and a dropout rate of 25% with a statistical power of 0.8, the sample size needed for each group is 64.

Previous community physical activity intervention studies using various recruitment methods, including utilisation of the AEC federal electoral roll, report a recruitment rate of 10-20% [20,24]. Therefore it was estimated that approximately 2000 letters need to be sent in the first mail out to recruit a suitable sample size.

### Statistical methods

Data will be analyzed according to group assignments, regardless of how many participants actually complete the study, the intent-to-treat principle. A maximum of four attempts will be made to contact participants that did not comply with the intervention protocols so outcome measures can be obtained, making the analysis more complete [37].

An intention-to-treat analysis may result in an underestimate of treatment effect, making it harder to find a significant difference [37]. Therefore data will be analyzed using both intention-to-treat and on-protocol analyses to determine if the two methods yield the same or different results. This justifies the allowance of a 25% drop-out rate.

Significance level will be set at *p *< 0.05. All analyses will be conducted using SPSS version 18.0.

### Randomised control trial

The primary analysis for the RCT will use repeated measures analysis of covariance (ANCOVA). All analyses will be adjusted for baseline values. Additional covariates to be considered include: gender, age and employment status, an ordinal measurement.

### Other analyses

A subsidiary comparison with the group exercise program will use the ANCOVA as described above, with the addition of the third intervention group.

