### Intervention

(i) Home-based intervention

Assessments for the home based program in this study will be conducted in participant's homes eliminating a number of barriers to physical activity adoption as discussed earlier [24]. Participants will be encouraged to invite a support person to attend during their initial assessment. After baseline measures are completed motivational interviewing will be used to devise an individual physical activity program [25]. A physiotherapist will discuss type, frequency, intensity, duration, benefits, barriers, goals, self-monitoring and progression of physical activity, aiming to achieve 30 min of moderate intensity physical activity most days of the week. Participants will be contacted by a physiotherapist via phone providing advice and support 2 weeks after the initial assessment and then monthly over a 6 month period, a total of approximately 6 phone calls.

(ii) Usual Care

Participants randomised to usual care will be visited by the physiotherapist in their homes. Baseline measures for the study will be completed giving participants an indication of their fitness and health status. Participants will receive two brochures 'An active way to better health. National Physical Activity Guidelines for Adults' and 'Dietary Guidelines for Australian Adults' from the Department of Health and Ageing [26,27]. They will not receive any other advice or support for increasing exercise or physical activity levels.

(iii) Group exercise program

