Participants in the group based program will attend the YMCA for their baseline measures. Baseline measures will be conducted by the same physiotherapist as the home based interventions. Participants will then have a choice of times for the group based exercise program which will be during business hours replicating similar programs and times offered in this community setting. These sessions will be run by a YMCA fitness instructor at the YMCA once a week, for 60 min, over 6 months. The exercise program will involve upper and lower body strengthening exercises, gross motor skill training and aerobic fitness training. The exercise specifics will be at the discretion of the YMCA fitness instructor, with no involvement from the physiotherapist, aiming to mimic 'usual practice'. Participants will be encouraged to increase their physical activity slowly and gradually in whichever way they prefer outside of the group sessions by the YMCA fitness instructors, aiming to achieve 30 min of moderate intensity physical activity most days of the week. An individual home based exercise program will not specifically be designed for this group.

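### The home-versus-group ANCOVA treats group-exercise participants as independent although they exercise in shared classes, so its standard error is too small if classmates' outcomes are correlated

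*Protocol article*

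**What the plan says.** The protocol article describes two forms of delivery. In the group arm (Intervention, part iii), "These sessions will be run by a YMCA fitness instructor at the YMCA once a week, for 60 min, over 6 months". There is more than one class time: "Participants will then have a choice of times for the group based exercise program". Content is not standardised: "The exercise specifics will be at the discretion of the YMCA fitness instructor". In the home arm (Intervention, part i) delivery is individual: "After baseline measures are completed motivational interviewing will be used to devise an individual physical activity program", followed by telephone calls to each participant.

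The model for the randomised comparison (Randomised control trial) is a repeated measures ANCOVA adjusted for baseline. Beyond baseline, "Additional covariates to be considered include: gender, age and employment status, an ordinal measurement". The section Other analyses then carries this model over to the group arm: "A subsidiary comparison with the group exercise program will use the ANCOVA as described above, with the addition of the third intervention group". Neither section mentions class, session time or instructor.

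The comparison is labelled subsidiary, but hypotheses 3 and 4 in the Background set home against group. The sample size also starts from a study "reporting a 20% difference in adherence to physical activity between a group and home based intervention at 12 months".

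**The concern.** People who attend the same class share an instructor, the content that instructor chooses, a time slot they selected themselves, and one another's company. Their outcomes may therefore be more alike than those of people in different classes. The repeated measures part of the ANCOVA handles correlation between visits of one person, not between classmates. A fixed effect for arm does not handle it either. The home arm has no classes, so the problem sits on one side of the contrast.

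If the within-class ICC is positive, the variance of the group-arm mean is understated. The home-group interval is then too narrow and its p-value too small. Hypothesis 4, that home participants are more likely to keep up their activity than group participants, would be tested with more than the stated 5% error. Estimates bearing on hypothesis 3, similar health benefits in the two programs, would look more precise than they are.

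**Working it through.** **Inputs from the article.** Difference 20 percentage points, SD 35, dropout 25%, power 0.8, 64 per group (Sample size); significance level 0.05 (Statistical methods). Sidedness is not stated; two-sided reproduces the figure.

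**Inputs assumed, because the article gives none.** 3 to 6 classes, 48 to 64 people in the group arm, ICC 0.01 to 0.05. Average class size m then runs from 48/6 = 8 to 64/3 = 21.3.

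**Step 1. The plan's own figure.** n per arm = 2 × 35² × (1.96 + 0.842)² / 20² = 48.07, and 48.07/0.75 = 64.1. The stated 64 is reproduced by a formula that takes people as independent in both arms, with no design effect.

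**Step 2. Variance with classes in one arm.** With equal arms of n:

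- planned: Var = (SD²/n) × 2
- correct: Var = (SD²/n) × (1 + DE), where DE = 1 + (m − 1) × ICC applies to the group arm only
- SE ratio r = √((1 + DE)/2)
- shortfall of the planned SE = 1 − 1/r
- true two-sided error of the nominal 5% test = 2 × (1 − Φ(1.96/r))

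**Step 3. Results.**

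| Classes × size | ICC | DE | r | Planned SE too small by | True error |
|---|---|---|---|---|---|
| 6 × 8 | 0.01 | 1.07 | 1.017 | 1.7% | 5.4% |
| 4 × 16 | 0.02 | 1.30 | 1.072 | 6.7% | 6.8% |
| 3 × 21.3 | 0.05 | 2.02 | 1.228 | 18.6% | 11.1% |

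Last row in full: DE = 1 + 20.33 × 0.05 = 2.02; r = √(3.02/2) = 1.228; 1.96/1.228 = 1.596; error = 11.1%.

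**Step 4. In percentage points of adherence.** With 48 per arm the planned SE is 35 × √(2/48) = 7.14, a 95% half-width of 14.0; the first row widens this to 14.2. With 64 per arm the planned SE is 35 × √(2/64) = 6.19, a half-width of 12.1; the second row gives 13.0 and the third 14.9.

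**Step 5. Power once classes are allowed for.** With 48 completers per arm, power for 20 points is 79.9% under independence. It is 78.6% with 6 classes of 8 and ICC 0.01, and 66.5% with 3 classes of 16 and ICC 0.05 (DE 1.75, r 1.173).

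These figures use a normal approximation, equal SDs and equal arms. At ICC = 0 nothing changes.

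**The case against.** **Left to the analysis plan.** A condensed article need not spell out every model term, and its covariate list is only of terms to be considered. This has some force, but the article does more than stay silent: it names the model and says the group arm will be added to it. Considering gender, age and employment status does not deal with correlation between classmates.

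**Weak mechanism.** Adherence is measured as all diary sessions against 20 or more a month over 2 years (Outcome measures). A weekly class supplies about 4 of those 20 and stops at month 6, leaving 18 of 24 months without classes. The instructor's discretion covers exercise content, and activity outside class is whatever the participant prefers. Fixed class membership is not stated, and people may switch times. If one instructor took every class, shared content would be part of the treatment rather than a source of between-class variation. All this stands and points to the low end of the range. Self-selection into class times could push the ICC the other way.

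**Larger problems elsewhere.** Allocation to group exercise is not randomised, and the Discussion says this limits attribution. That is probably the greater weakness. It concerns bias, however, and correcting one problem does not correct the other.

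**Stronger readings a reader might infer.**

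- *That hypothesis 5 takes its error from this ANCOVA.* It does not: Cost-effectiveness analysis uses a bootstrapped cost-effectiveness ratio, with a similar analysis for home versus group.
- *That a formal equivalence test for hypothesis 3 is invalidated.* The article states no margin and no interval-based test, so only the precision of the estimates is affected.
- *That an SE ratio of 1.23 means the planned SE is 23% too small.* The correct SE is 23% larger; the planned one is 1 − 1/1.228, about 19%, too small.
- *That the randomised result or the figure of 64 is thereby wrong.* Home and usual-care participants do not attend classes, and the documents give no ICC from which a larger sample could be derived.

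**Conclusion.** The point holds for the non-randomised home-versus-group comparison only. The direction follows from the design and the stated model: for any positive within-class ICC, the planned standard error is too small. The size rests on assumed class numbers, class sizes and ICCs. Over the assumed range, the true error of a nominal 5% test runs from barely above nominal to about double. A modest excess is more plausible than the upper end, which needs three large classes and an ICC of 0.05 together. The correction is still worth making: two hypotheses use this contrast, the remedy is cheap, and class attendance cannot be reliably reconstructed if it is not recorded while the classes run.

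**What to change.** 1. Record the class and the instructor that each group participant mainly attends.
2. For the home-group comparison (hypotheses 3 and 4), replace the plain three-group ANCOVA with a partially nested mixed model: a class random effect in the group arm only, with small-sample degrees of freedom.
3. If there are too few classes to estimate the class variance, keep the ANCOVA, report the home-group interval multiplied by r for ICCs of 0.01 to 0.05 at the observed class sizes, and state clustering as a limitation.
4. For hypothesis 5, deal with class inside the home-group bootstrap, for example by resampling whole classes if there are enough of them.
5. Leave the randomised home-versus-usual-care analysis as it is.

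**Cost.** Two recorded items and one model term, with no extra participants and no change to either program. The home-group intervals will be wider. With 3 to 6 classes the class variance would rest on roughly 2 to 5 degrees of freedom and be imprecise, so the fallback in item 3 may well be what is reported.

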### Cost-effectiveness analysis

Cost components for recruitment of participants and cost of the interventions will be recorded prospectively during the 2 year study period. Cost items include participant travel costs and resource use, for example, hospitalisations and GP visits, which will be collected via the 6-monthly questionnaires over the 2 year period. This data will be used in conjunction with an estimate of the health benefits, measured in terms of Disability Adjusted Life Years (DALYs), to undertake a cost-effectiveness analysis comparing the two arms of the study. Disability adjusted life years will be estimated using the method developed by Murray [38]. Health status will be measured using preference-based health status scores derived from individual SF-12 questionnaire responses [39]. The cost-effectiveness analysis will be conducted prospectively alongside the trial to compare costs per DALY change in the trial arms. Cost-effectiveness will be calculated as the ratio of the difference in costs between the home based physical activity program and usual care divided by the difference in DALYs between the two groups. The non-parametric bootstrap method (using 1000 replications) will be used to derive confidence intervals for the incremental cost-effectiveness ratio (ICER) over the follow-up period [40]. Cost-effectiveness acceptability curves [41] will be constructed from these data to provide estimates of the probability that, for a given level of the cost per DALY--the so-called 'ceiling' level, the home based physical activity program is more cost-effective than usual care.

Similar analysis will be conducted to compare cost-effectiveness between the home based interventions and the group exercise program.

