### Outcome measures

The methods of participant assessment have been carefully considered as assessments are taking place in people's homes. All study measures will be assessed at baseline, 6, 12, 18 and 24 months.

The main outcome measure of this study is long term adherence to physical activity. Adherence will be measured using exercise diaries completed over the 2 year study period, a continuous measure. Exercise diaries have been found to be both reliable and valid [28]. Participants will be encouraged to record date, type, duration and intensity, using the modified Borg rating of perceived exertion scale (RPE) [29], every time they are physically active. Participants will be encouraged to return the diaries in the supplied prepaid envelope at the end of each month over the study period.

Average monthly adherence rates across the 2 year period will be calculated as follows: number of physical activity sessions reported as a percentage of physical activity sessions prescribed for the month. This is similar to the method described by King [20] to determine adherence rates to different physical activity intensities and formats over a 2 year period. The number of sessions prescribed for the month will be based on the World Health Organisation (WHO) physical activity guidelines [3]. That is, 30 min of moderate intensity physical activity, five or more days per week, a total of 20 or more sessions per month. Thirty minutes can be accumulated in 10 min bouts of physical activity per day. Moderate intensity is defined as a rating of 3 or more on the modified Borg RPE scale.

Secondary outcomes include the Active Australia Survey (AAS), accelerometry, aerobic capacity (2 min step test), quality of life (SF-12v2) and disease biomarkers, that is, waist circumference (cm), waist:hip ratio (WHR), blood pressure (mmHg) and body mass index (BMI, kg/m^2^).

The AAS and accelerometry will be used to validate the data collected from the exercise diaries. These two continuous measures will be collected every 6 months over the 2 year study period.

The AAS has been designed to measure participation in leisure time physical activity and to assess the participant's knowledge of current public health messages about the health benefits of physical activity. It offers a short and reliable set of questions and applies to 1 week preceding the interview, including walking for transport. The AAS has been reported as reliable and of acceptable validity [30,31].

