Covering the same time period as the AAS, participants will wear an Actigraph GT1M accelerometer [32] for 7 consecutive days. Accelerometers allow an objective measurement of quantity and intensity of movement and have been found to be reliable and valid [33].

The raw data collected by the accelerometer, counts, will be used to obtain the time spent in different physical activity intensities [34]. We will use the Freedson Combination energy expenditure algorithm to determine the intensity cut-points [32]. This outcome variable will be used to investigate whether participants have reached the WHO physical activity guidelines.

Assessment of aerobic capacity is essential to determine whether the completed physical activity has been intense enough to result in an improvement in cardiovascular fitness. The 2 min step test requires little space and equipment, with large studies finding it both reliable and valid [35]. The 2-minute step test protocol involves determining the number of times in 2 min that a person can step in place raising the knees to a height halfway between the patella (kneecap) and iliac crest (front hip bone), a continuous measurement. Only one successful trial will be administered.

The SF-12v2 is a general health status questionnaire which has a 12-item scale producing eight separate sub-scales (physical functioning, physical role functioning, emotional role functioning, social functioning, bodily pain, mental health, vitality and general health perceptions) to assess quality of life [36]. It takes the participant less than 2 min to complete the tool and is a quasi-continuous measurement.

Waist circumference and hip circumference will be measured in centimetres using a tape measure. Blood pressure levels will be obtained using a mercury sphygmomanometer on the right arm of seated subjects. Both measures will be taken twice and then the average will be recorded. BMI (kg/m^2^) will be recorded using a portable set of scales and a stadiometer.

Sociodemographic information will also be collected with questions regarding participant's education level, relationship status, current employment status and the presence of any chronic diseases.

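### The economic analysis divides by DALYs but names only SF-12 preference scores as its health measure, with no link or direction stated, and its bootstrap interval for the ICER may not be interpretable

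*Protocol article*

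**What the plan says.** All of the following is in the protocol article.

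- **Effect measure (Cost-effectiveness analysis).** Costs are to be set against "an estimate of the health benefits, measured in terms of Disability Adjusted Life Years (DALYs"). On the method: "Disability adjusted life years will be estimated using the method developed by" the author of a cited source. No disease, disability weight or model is named.
- **Health status (same section, next sentence).** "Health status will be measured using preference-based health status scores derived from individual SF-12 questionnaire responses". QALYs are not mentioned anywhere.
- **Ratio (same section).** The cost difference between the home based program and usual care is "divided by the difference in DALYs between the two groups".
- **Uncertainty (same section).** "The non-parametric bootstrap method (using 1000 replications) will be used to derive confidence intervals for the incremental cost-effectiveness ratio". The type of bootstrap interval is not given. Acceptability curves are planned from the same data, and a similar analysis is to compare home with group.
- **Other health data.** The Outcome measures section lists "disease biomarkers, that is, waist circumference (cm), waist:hip ratio (WHR), blood pressure (mmHg) and body mass index", and its sociodemographic questions cover "current employment status and the presence of any chronic diseases". Hospitalisations and GP visits are recorded in the economic section as resource use. None of these is tied to DALYs.
- **Size (Sample size).** 64 per group, allowing for 25% dropout, based on adherence alone.

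**The concern.** DALYs and SF-12 preference scores belong to different constructions. A DALY adds years of life lost to time in disease states weighted by disability. A preference score is a utility, and its area under the curve over time is a QALY. The section names one as the effect and the other as the measurement, so an analyst cannot tell which quantity goes into the denominator. DALYs also count a loss, and the text does not say whether the difference is DALYs averted or a plain difference between arms.

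The second part is the interval. A ratio changes sign and becomes very large in absolute value as its denominator passes through zero. If bootstrap replicates of the effect difference lie on both sides of zero, sorting the ratios mixes replicates from opposite quadrants of the cost-effectiveness plane, and percentile limits lose their meaning.

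The economic conclusions are at stake: the comparison with usual care and, through the similar analysis, the home versus group claim in hypothesis 5 (Background). The undefined effect and direction would also carry into the acceptability curves.

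**Working it through.** **1. The plan's own figure.** Inputs from Sample size: difference 20 percentage points, SD 35, power 0.80, dropout 25%. The 0.05 level is from Statistical methods, and two-sided is assumed.

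n = 2 × [35 × (1.960 + 0.842) / 20]² = 48.07 per group; 48.07 / 0.75 = 64.1. The stated 64 is reproduced. Rounding up first gives 49, then 66. After 25% dropout, 64 × 0.75 = 48 per arm remain. No corresponding figure is given for DALYs, utilities or costs.

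**2. What the available data yield.** With utilities u at 0, 6, 12, 18 and 24 months, half a year apart, the trapezoid rule gives

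QALY = 0.5 × (u0/2 + u6 + u12 + u18 + u24/2).

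This needs nothing beyond the SF-12 already scheduled. A DALY would need disability weights and years of life lost, and the article identifies no trial variable as their source.

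**3. Direction.** Write ΔC for the cost difference and ΔD for the DALY difference, both home minus usual care. If the program costs more and helps, ΔC > 0 and ΔD < 0, so the ratio is negative. If the effect is DALYs averted, −ΔD, the same result has a positive ratio. A positive ceiling cost per DALY on the acceptability curve makes sense only under the second convention.

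**4. How often the denominator straddles zero.** Let d be the true effect difference divided by its SD. This is an assumption, shown as a range. With n per arm, the SE in SD units is √(2/n), so for n = 48 the 95% half-width is 1.96 × √(2/48) = 0.40 SD. For n = 64 it is 0.35 SD. The probability that the 95% interval includes zero is

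1 − [Φ(d√(n/2) − 1.96) + Φ(−d√(n/2) − 1.96)].

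| d | 48 per arm | 64 per arm |
|---|---|---|
| 0.1 | 92.2% | 91.3% |
| 0.2 | 83.5% | 79.5% |
| 0.3 | 68.8% | 60.4% |
| 0.4 | 50.0% | 38.1% |
| 0.5 | 31.2% | 19.3% |
| 0.571 (= 20/35, the effect assumed for adherence) | 20.1% | 10.2% |

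Example: n = 48, d = 0.1 gives d√24 = 0.490, and 1 − [Φ(−1.470) + Φ(−2.450)] = 0.922.

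**5. Bootstrap check.** Normal data were simulated, with 200 trials per setting and 1000 replicates per trial. At d of 0.1 to 0.2, on average about 21% to 38% of replicates had a denominator at or below zero, across both arm sizes. At d = 0.4 it was about 5% to 8%.

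**The case against.** The strongest reply is that this is a journal article. It cites sources for the DALY method, the SF-12 scoring, the bootstrap and the curves. A fuller economic plan may say how the scores enter the DALY estimate, and a missing mapping would not by itself be an error. That much stands. What remains is that the current text names two different effect quantities in consecutive sentences and does not reconcile them.

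Four stronger readings are tempting, and the documents do not support them.

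- **That SF-12 scores are the only individual health data.** Chronic disease, blood pressure, waist measures, BMI and hospitalisations are also collected. The accurate statement is that SF-12 scores are the only health status measure the economic section names.
- **That the denominator is certain to span zero.** No SD or expected effect is given. Spanning zero is likely for small effects, a coin toss at d = 0.4 with 48 per arm, and the less likely outcome at 0.5 and above. The variance of DALYs under the cited method is unknown.
- **That the ratio is wrongly signed.** The section speaks of health benefits and a ceiling cost per DALY, which is compatible with DALYs averted. The direction is unstated, not shown to be wrong.
- **That moving to QALYs cures the quadrant ambiguity.** Costlier and better, and cheaper and worse, share a sign in any ICER. Net benefit and the plane resolve this; a change of effect measure does not.

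It is also fair that part of the remedy is already planned: acceptability curves handle all four quadrants if they are computed from net benefit.

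**Conclusion.** The point holds in two parts. First, the section leaves the effect measure and its direction unresolved between DALYs and SF-12 preference scores. This rests on the text alone. Second, the planned interval for the ICER carries a substantial risk of being uninterpretable in a trial sized only on adherence. With 48 per arm, the probability that the denominator's 95% interval includes zero falls from 92.2% at d = 0.1 to 31.2% at d = 0.5. Those figures assume approximate normality, equal SDs, 25% dropout and the stated values of d, none of which the documents supply for this outcome except the dropout rate. Small effects are plausible, since the Participants section recruits people aged 50 to 65 without serious medical conditions, but this is a judgement.

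The issue is confined to a secondary analysis. The interval problem affects only the ICER interval; the undefined effect measure also reaches the acceptability curves. It should be settled before the economic data are analysed.

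**What to change.** 1. **Define one effect measure.** Make it QALYs gained: the area under the SF-12 preference score curve over the five visits, adjusted for baseline utility. If DALYs are kept, define them as DALYs averted and state the model, its inputs and the order of subtraction.
2. **Replace the ICER confidence interval.** Report incremental net monetary benefit, λ × ΔE − ΔC, where ΔE is QALYs gained or DALYs averted, with a bootstrap 95% CI at stated thresholds λ. It involves no division, so replicates on both sides of zero cause no difficulty. The ICER can still be given as a point estimate.
3. **Show the cost-effectiveness plane, and build the planned acceptability curves from net benefit.**
4. **Apply the same definitions to home versus group.** That comparison remains non-randomised.

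The cost is a little more analysis and an amended economic section. Moving to QALYs changes the declared economic effect measure, so it should be recorded as such, and it reduces comparability with DALY-based studies. No new data are needed for the QALY option.

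### The cost-effectiveness section names no baseline adjustment for its ICER, which costs precision for home versus usual care and leaves home versus group open to confounding by starting health

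*Protocol article*

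**What the plan says.** Under Cost-effectiveness analysis, the protocol article defines the ICER for the randomised comparison as follows: "Cost-effectiveness will be calculated as the ratio of the difference in costs between the home based physical activity program and usual care divided by the" matching difference in DALYs. On the health input it says: "Health status will be measured using preference-based health status scores derived from individual SF-12 questionnaire responses". On uncertainty: "The non-parametric bootstrap method (using 1000 replications) will be used to derive confidence intervals for the incremental cost-effectiveness ratio (ICER"), with acceptability curves built from the same data. The section also says that the aim is to "compare costs per DALY change in the trial arms", without defining that phrase. The non-randomised contrast gets one sentence: "Similar analysis will be conducted to compare cost-effectiveness between the home based interventions and the group exercise program".

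Baseline adjustment appears elsewhere. Under Randomised control trial, straight after the repeated measures ANCOVA is named, the article says "All analyses will be adjusted for baseline values" and lists gender, age and employment status as further covariates to consider. Under Other analyses it extends that model: "A subsidiary comparison with the group exercise program will use the ANCOVA as described above, with the addition of the third intervention group".

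The data needed for adjustment exist. Under Outcome measures: "All study measures will be assessed at baseline, 6, 12, 18 and 24 months", and the SF-12v2 is one of those measures.

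**The concern.** A participant's health score at entry usually predicts the scores that follow. If arms differ at entry and the health difference is not adjusted, part of the starting difference is counted as program effect in the denominator of the ICER. The bootstrap resamples participants as they are, so it does not remove a difference between the groups.

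The consequence differs by contrast. For home versus usual care, randomisation balances starting health on average, so the loss is precision: a wider ICER interval and a flatter acceptability curve than necessary.

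For home versus group, participants sort themselves. Under Recruitment, the second letter goes to people who were not interested in the group program. The Background says that lonely or depressed people may be less suited to groups, and the SF-12v2 has mental health and social functioning sub-scales. Group sessions run in business hours, which may select on employment. Unequal starting health is therefore plausible, and hypothesis 5 is a cost-effectiveness claim about exactly this contrast. The clinical comparison of the three groups is baseline-adjusted, so as written the economic comparison is less well protected than the clinical one.

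**Working it through.** **Does the stated adjustment reach the ICER?**

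- The baseline sentence stands under the heading for the RCT and follows the ANCOVA.
- Where the authors wanted that model again, under Other analyses, they referred back to it.
- The economic section has its own heading, makes no such reference and gives a different estimator.
- A DALY total over follow-up has no baseline value of its own. The natural covariate is the baseline SF-12 preference score, which is never named as one.

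The plan as written therefore leads an analyst to an unadjusted ratio, although it does not use that word.

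**Inputs for an illustration.** The documents give no ICER, DALY, SF-12 standard deviation or between-visit correlation to reproduce. The group size is the only usable figure. From Sample size (difference 20, SD 35, power 0.8), with two-sided alpha 0.05 assumed: 2 × (35 × (1.960 + 0.842)/20)² = 48.07, and 48.07/0.75 = 64.1, which matches the stated 64. I use 48 (after dropout) and 64 per arm.

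Assumed, not from the documents:

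- a two-year health total by the trapezoid rule over 0, 0.5, 1, 1.5 and 2 years, with weights w = (0.25, 0.5, 0.5, 0.5, 0.25);
- equal variance and equal correlation ρ between visits;
- a preference-score SD of 0.12 where one is needed (range 0.08 to 0.15).

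**Precision.** In units of the score variance, Σw² = 0.875 and (Σw)² = 4, so:

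- Var(total) = 0.875(1 − ρ) + 4ρ
- Cov(total, baseline) = 0.25 + 1.75ρ, which is also the slope of the total on baseline
- share of variance left after adjustment = 1 − Cov²/Var(total)

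| ρ | Var(total) | Slope | Correlation with baseline | Variance left | SE reduction |
|---|---|---|---|---|---|
| 0.3 | 1.8125 | 0.775 | 0.58 | 67% | 18% |
| 0.5 | 2.4375 | 1.125 | 0.72 | 48% | 31% |
| 0.7 | 3.0625 | 1.475 | 0.84 | 29% | 46% |

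**Chance imbalance, home versus usual care.** The SE of the baseline difference is 0.12 × √(2/n) = 0.0245 (n = 48) or 0.0212 (n = 64). At ρ = 0.5 a one-SE imbalance moves an unadjusted total by 1.125 × 0.0245 = 0.028 or 1.125 × 0.0212 = 0.024 health-years. Over SD 0.08 to 0.15 and ρ 0.5 to 0.7 the range is 0.016 to 0.045. This is sampling variation.

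**Self-selection, home versus group.** Suppose the groups differ by 0.03 at baseline (assumed). At ρ = 0.5 the part predicted by baseline is 0.03 × 1.125 = 0.034. If the difference persists in full for two years, the total differs by 0.03 × 2 = 0.06. Regression on baseline then removes 0.034 and leaves 0.026, or 44%.

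**If the change phrase means change from baseline.** Subtracting 2 × baseline from the total gives a slope on baseline of (0.25 + 1.75ρ) − 2 = −0.875 at ρ = 0.5 and −0.525 at ρ = 0.7. The result still depends on baseline, with the sign reversed.

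**The case against.** The strongest reply is that the plan never calls the differences raw. Every ICER, adjusted or not, is a ratio of two differences; the baseline sentence says all analyses; and a condensed article may leave the regression to a fuller plan. A reader might infer that the protocol defines an unadjusted ICER or rules adjustment out. The text does not support that. What stands is narrower: the section specifies an estimator and its bootstrap, names no baseline term, and does not refer back to the ANCOVA as the neighbouring section does.

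A reader might also infer that chance imbalance biases the home versus usual care result. It does not. The unadjusted estimate is unbiased over randomisation, and the bootstrap interval carries that variation.

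The illustration is open to challenge too. The article mentions no trapezoid total, and DALYs follow a cited method that is not shown. The trial is powered on adherence, so no power claim for DALYs is made here, and the variance figures concern the health difference only, not the costs or the ratio.

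Finally, a reader might infer that a baseline covariate would cure self-selection. It would not: in the fully persistent case above, 44% of the difference remains, and a change score would do better in that case. Selection on costs or motivation would also remain. The article itself calls the three-way comparison quasi-experimental under Design and lists the lack of randomisation as a limitation in the Discussion. That limits the claim but does not justify leaving out an adjustment for data already collected.

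**Conclusion.** The concern holds in a limited form. Taken as written, the economic analysis does not use the baseline SF-12 score. For home versus usual care this is lost precision, not bias. For home versus group it is confounding by any baseline health difference, in the contrast on which hypothesis 5 rests.

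The size is illustrative only. The 67% to 29% of variance remaining depends on the assumed trapezoid total and equal correlations of 0.3 to 0.7. The shifts in health-years depend also on an assumed SD, or on an assumed group difference. Whether any real imbalance would change the cost-effectiveness conclusion cannot be told from the documents. The primary adherence analysis is not affected. The change is worth making because it is a better use of data already planned and costs almost nothing. If adjustment was always intended, the same wording settles the ambiguity.

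**What to change.** In Cost-effectiveness analysis, add wording to this effect:

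- Incremental DALYs (built from the SF-12 preference scores) and incremental costs are each estimated by regression on arm and baseline SF-12 preference score.
- For home versus group, the models also include the covariates already listed under Randomised control trial: gender, age and employment status.
- Both regressions are re-fitted within each of the 1000 bootstrap replications, so that the ICER interval and acceptability curves use the adjusted increments.
- The unadjusted ratio is reported as a sensitivity analysis.
- Adjustment removes only measured baseline differences, so home versus group remains quasi-experimental.

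The authors should also define what a DALY change means.

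The cost is a few sentences and a little programming, with no new data, visits or staff. There are two small downsides: participants without a baseline SF-12 need a simple imputation of that covariate, and the adjusted ratio is slightly less transparent than the unadjusted one.
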